**Sample size and justification**

In each arm of the study 1,400 youth will be recruited for a total of 2,800 participants. The intervention arm will include 1,000 ISY and 400 OOSY, and the control arm will also include 1,000 ISY and 400 OOSY.

The sample size calculation is based on the frequency of intervention endpoints, the effect size of the intervention, the cluster design and related design effect, as well as expected cohort attrition rate all calculated in the school sample.

We assume a cluster size of 25, an intra-class correlation of 0.15 and 20% attrition per cluster.

The power calculation for contraception is calculated among the girl sample (cluster of 10 girls per school accounting for the 20% attrition). Baseline contraceptive prevalence in Kinshasa among 15-17 year old adolescents is 13%, based on recent PMA2020 data collected in 2016. A cluster sample of 500 adolescents per group (40 clusters) will detect a doubling of contraceptive prevalence in the intervention arm with a power of 79%. The pregnancy rate of 5% based on PMA2020 estimate is too low to be able to detect a difference between intervention and control groups in this study.

Calculations were done using the Stata clustersampsi command for the two primary outcomes:

- Contraception: clustersampsi, binomial samplesize p1(0.13) p2(0.26) k(80) rho(0.2) alpha(0.05) beta(0.8)
- GBV: clustersampsi, binomial samplesize p1(0.10) p2(0.05) k(40) rho(0.02) alpha(0.05) beta(0.8)

All other indicators including attitudinal and knowledge measures are based on continuous scores. Calculations based on preliminary results from the gender norms scales from the pilot GEAS in Kinshasa indicate that a sample size of 800 adolescents (40 clusters of 20 adolescents each, after attrition) is sufficient to detect a 10% shift in the gender scores between the intervention and control groups.

Table 3. Sample size calculation

| **Endpoints** | *Control* | ***Effect size*** | *Intra-class correlation* | ***Power*** | ***N clusters /arm*** | ***Minimum average students/ cluster*** | ***N participants / arm*** |
| --- | --- | --- | --- | --- | --- | --- | --- |
| **Attitudes** |  |  |  |  |  |  |  |
| Stereotypical gender norms (continuous score 13 to 62) | *Scale 1 Mean=3.99*  *SD=0.59*  *Scale 2*  *Mean=3.55*  *SD=0.69* | *Scale 1 detectable different =0.14*  *Scale 2 detectable different =0.17* | *0.15* | *80%* | *40* | *20* | *800* |
| Discussed contraception | *6%* | *RR=2.5* | *0.20* | *76%* | *40* | *20* | *800* |
| **Behavioral** |  |  |  |  |  |  |  |
| Proportion using modern contraception | *13%* | *RR=2* | *0.2* | *79%* | *40* | *11* | *440 girls* |
| Pregnancy | *5%* | *RR=0.5* |  | *27%* | *40* | *20* |  |
| Exposure to gender based violence in the last 6 Months (dichotomous) | *10%* | *RR=0.5* | *0.2* | *0.98* | *40* | *20* | *560* |

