This longitudinal phase builds on the first by exploring how gender norms relate to health across the adolescent years, beginning with early adolescence. The GEAS in Kinshasa has two sets of objectives: 1) To explore how perceptions of gender norms evolve across adolescence, the factors influencing these changes, and how perceptions of gender norms predict a spectrum of adolescent outcomes, and 2) Assess the impact of a gender norms transformative intervention developed and implemented by Save the Children. The intervention, Growing Up GREAT (GUG), and evaluation components are part of a larger project, *Passages*, which is led by the Institute for Reproductive Health (IRH) at Georgetown University. Our research partner is the Kinshasa School of Public Health (KSPH), which will implement the GEAS study. The Kinshasa component of the project has both USAID and Gates Foundation support.

In both an intervention and control group 1,400 young people ages 10-14 will be followed over a period of 4 years, with one additional year of data analysis. To gauge effectiveness of the intervention, we will assess the following measurable primary and secondary study outcomes:

Primary outcomes:

- Doubling of contraception use among sexually active youth
- 10% decrease in reports of exposure to gender-based violence (GBV) compared with the previous 6 months

Secondary outcome:

- 20% shift toward more gender-equitable attitudes and beliefs

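### The stated 79% power for contraception is computed on all school girls, but the primary outcome is defined among sexually active youth

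*Protocol*

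**What the plan says.** Section I (Aims of the Study) lists as the first primary outcome: "Doubling of contraception use among sexually active youth". The restriction is to the sexually active. It is not limited to girls or to pupils.

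Section IV, under Sample size and justification, says that all calculations are made in the school sample. For contraception: "The power calculation for contraception is calculated among the girl sample (cluster of 10 girls per school accounting for the 20% attrition". The control rate is introduced as follows: "Baseline contraceptive prevalence in Kinshasa among 15-17 year old adolescents is 13%, based on recent PMA2020 data collected in 2016". The power is put at 79%, in the sentence that begins: "A cluster sample of 500 adolescents per group (40 clusters) will detect a doubling of contraceptive prevalence in the intervention arm with a power of".

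The printed command is "Contraception: clustersampsi, binomial samplesize p1(0.13) p2(0.26) k(80) rho(0.2) alpha(0.05) beta(0.8"). The Table 3 row reads "Proportion using modern contraception | *13%* | *RR=2* | *0.2* | *79%* | *40* | *11* | *440 girls". The general assumptions are: "We assume a cluster size of 25, an intra-class correlation of 0.15 and 20% attrition per cluster".

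The brief data analysis plan in section V.C, item 4, speaks of contraceptive use compared between the groups and mentions no restriction to the sexually active. The protocol gives no expected share of sexually active participants at any wave, for a cohort enrolled at ages 10 to 14 and followed for about four years.

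**The concern.** A power figure belongs to a defined set of people with a defined event rate. Here the outcome counts only sexually active youth, while the calculation counts every retained girl in the school sample. Restricting the set changes the number analysed. It may also change the rates, because contraceptive prevalence among the sexually active need not equal prevalence among all girls of that age.

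This is one of two primary outcomes, and 79% is the only power figure offered for it. If it describes a different comparison, the sponsor does not know whether the study can answer its first question. Two smaller discrepancies in the same paragraph and table (80 or 40 clusters, 10 or 11 girls per school) make the calculation harder to audit.

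**Working it through.** **Inputs from the protocol:** p1 = 0.13, p2 = 0.26, intra-class correlation 0.2 for this outcome, alpha 0.05 (taken as two-sided), 40 schools per arm, 10 girls per school after attrition (text) or 11 (Table 3). **Assumed, because the protocol gives none:** the sexually active share f, shown as a range.

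**Formulas.** Effective number per arm: n_eff = n / DE, where n is the number analysed per arm and DE the design effect, DE = 1 + (m − 1) × 0.2 for m per school. Power = Φ{[(p2 − p1)√n_eff − 1.96 √(2p̄(1 − p̄))] / √(p1(1 − p1) + p2(1 − p2))}, with p̄ the mean of the two rates.

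**1. Reproducing the 79%.** For 13% against 26%, p̄ = 0.195, √(2 × 0.195 × 0.805) = 0.5603 and √(0.1131 + 0.1924) = 0.5527.
- 10 girls per school: DE = 1 + 9 × 0.2 = 2.8; n_eff = 400/2.8 = 142.9; z = (0.13 × 11.95 − 1.96 × 0.5603)/0.5527 = 0.824; power 79.5%.
- 11 girls per school: DE = 3.0; n_eff = 440/3.0 = 146.7; power 80.6%.

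The stated figure is thus recovered by counting every retained school girl. With the general correlation of 0.15 and 10 girls, the result would be 86.0%, so the 79% goes with 0.2.

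**2. 13% against 26% among sexually active school girls.** If a share f of the 10 girls per school is sexually active and the number varies at random between schools, n = 400f and DE = 1 + 9 × f × 0.2.

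| f | n per arm | DE | n_eff | Power |
|---|---|---|---|---|
| 50% | 200 | 1.90 | 105.3 | 67% |
| 30% | 120 | 1.54 | 77.9 | 54% |
| 20% | 80 | 1.36 | 58.8 | 43% |
| 10% | 40 | 1.18 | 33.9 | 27% |

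A beta-binomial simulation with a cluster-robust test (4,000 runs per share) gave 67%, 54%, 44% and 31%, and 79% at f = 100%.

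**3. 13% as the prevalence among all girls.** If every user is sexually active, the rates in the restricted set are 0.13/f and 0.26/f. This requires f of at least 26%.
- f = 75%: 17.3% against 34.7%, n_eff = 300/2.35 = 127.7, power 89%.
- f = 50%: 26% against 52%, n_eff = 200/1.90 = 105.3, power 98%.

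**4. Sexually active school boys also count.** With 20 retained pupils per school, n = 800f and DE = 1 + 19 × f × 0.2. At 13% against 26%, n_eff is 137.9, 112.1, 90.9 and 58.0 at f = 50%, 30%, 20% and 10%. Power is 78%, 69%, 60% and 42%.

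**5. Out-of-school youth also count.** Adding 400 × 0.8 = 320 retained out-of-school youth per arm to case 4, treated as unclustered (a best case), gives 83% at f = 20% and 60% at f = 10%.

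**6. Smaller inconsistencies.** For 80% power without clustering, n = 145 per arm. Solving k × m = 145 × (0.8 + 0.2m) for k clusters per arm gives m = 116/(k − 29). For k = 40 this is 10.5, rounded up to 11; for k = 80 it is 2.3, rounded up to 3. Table 3's 11 therefore belongs to 40 clusters per arm and not to the printed 80. The command for gender-based violence uses k(40) for the same schools. The text's 10 girls per school is below Table 3's minimum average of 11, a difference of about one point of power.

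**The case against.** The strongest reply is that the loss of power is not established. The 13% is worded as a prevalence among adolescents aged 15 to 17, with no restriction to the sexually active. Read that way, the rates in the restricted set are higher and power goes up (case 3). The outcome also says youth, so boys and the 400 out-of-school youth per arm may contribute, which recovers much or all of the loss (cases 4 and 5). All of this stands.

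A reader might therefore infer too much in several ways:
- That power for this outcome is far below 79%, or that 79% is reached only if every girl is sexually active. The first needs a 13% that applies to the sexually active, a small active share and an analysis limited to school girls; the second needs the first and third of these. The protocol states only the last, and only for the power calculation.
- That the 500 per group contradicts the 10 girls per school. It does not: 500/40 = 12.5 girls enrolled, and 12.5 × 0.8 = 10 retained.
- That a sex quota in the draw of 25 is needed. The stated power is met with 10 retained girls per school, which is what half of 25 gives after 20% loss.
- That the protocol is at fault for lacking a supporting analysis over all girls, or for not dealing with sexual activity being measured after the intervention. Both can be left to an analysis plan, which is not shown here.

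What the reply does not remove is the mismatch itself. The protocol defines the outcome on one set of people and prints the power for another.

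**Conclusion.** The point holds as a mismatch of denominators. The 79% is the power to compare 13% with 26% among all retained school girls. It is not the power for contraception use among sexually active youth.

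Neither the size nor the direction of the error can be fixed from the document. Across the readings that limit the comparison to school girls, power runs from about 27% (13% against 26% among the sexually active, share 10%) to about 98% (13% among all girls, all users sexually active, share 50%). Counting boys in the first reading gives about 42% to 78% at shares of 10% to 50%. These figures rest on assumed shares, an intra-class correlation of 0.2, 40 schools per arm, 20% attrition and a two-sided 5% test. The k(80) and the 10 or 11 girls are real but minor inconsistencies. The text and Table 3 both give 40 clusters per arm, and the 79% is reproduced there.

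**What to change.** Make the outcome and the power calculation use the same denominator. In the sample size section, state:
- whether the 13% refers to all adolescents aged 15 to 17 or to the sexually active among them;
- the sexually active share expected at the wave on which the outcome will be analysed;
- whether boys and out-of-school youth count towards the outcome.

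Then restate the contraception row of Table 3 for that denominator, with power over a range of the share. In the same edit, change k(80) to 40 clusters per arm and use one figure, 10 or 11, for girls per school.

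The cost is a revised paragraph, one table row and a repeated calculation. The edit itself changes neither recruitment nor data collection. The restated power may be less favourable than 79%, or more so, depending on the answers.

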|  | *Intervention*  *N=* | *Control*  *N=* | *Intervention*  *N=* | *Control*  *N=* |
| **Public, non-religious** | 9 | 5 | 16 | 1 |
| **Public, religious** | 20 | 14 | 24 | 41 |
| **Private** | 37 | 51 | 26 | 42 |

*In-school adolescent participants*

For both the intervention and control arms of the study, students will be invited to participate until 25 from each school assent (and whom have obtained parental consent). We will apply this predetermined cluster size to select the same number of students (n=25) per school in the intervention and control areas. Students in the control schools will be selected at random (from a list of all students between 10 and 14 years in the school), while those in the intervention area are self-selected based on their choice to participate in the intervention.

A total of 40 schools per study arm, equally distributed between Masina and Kimbanseke, will be selected. Altogether, 1,000 students will be enrolled in each school arm (intervention and control). Sample size calculation is detailed in the section, “Sample size and justification.”

*Parents of in-school adolescents*

All parents of in-school participants who consent their children to participate will be asked to participate in a baseline survey collecting sociodemographic information about themselves and household information.

*Out-of-school sample*

*Out-of-school adolescent participants*

Out-of-school participants will be recruited with the assistance of community-based organizations (CBOs) and religious organizations that work with OOSY in these communes. Specifically, KSPH will work with CBOs that serve out of school youth in each quartier and group (control or intervention) to create a list of eligible youth from which participants will be recruited. Youth whom have been out of school for 2 or more years will be prioritized due to the decreased likelihood that they will re-enroll in school during the study compared with youth who have been out of school for less time. A total of 400 out-of-school adolescents will be recruited in each arm of the GEAS cohort.

*Parents of out of-school adolescents*

All parents of out of-school participants will be asked to participate in a baseline survey collecting sociodemographic information about themselves and household information.

*Inclusion and exclusion criteria*

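### The contraception command prints 80 clusters where the design has 40 per arm, and Table 3 pairs the size needed for 80% power with the 79% power of a smaller size

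*Protocol*

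**What the plan says.** All of the following is in the Protocol.

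- **Design** (IV. Participants): "A total of 40 schools per study arm, equally distributed between Masina and Kimbanseke, will be selected".
- **General assumptions** (Sample size and justification): "We assume a cluster size of 25, an intra-class correlation of 0.15 and 20% attrition per cluster".
- **Girls per school** (same section): the contraception calculation is done in girls, with a "cluster of 10 girls per school accounting for the 20% attrition".
- **Stated power, 79%** (same section): the sentence that ends in this figure reads "A cluster sample of 500 adolescents per group (40 clusters) will detect a doubling of contraceptive prevalence in the intervention arm with a power of".
- **Command** (same section): after the proportions 0.13 and 0.26, the contraception line has "k(80) rho(0.2) alpha(0.05) beta(0.8" (closing bracket omitted here). The GBV command on the next line has k(40) and an ICC of 0.02.
- **Table 3, contraception row**: "Proportion using modern contraception | *13%* | *RR=2* | *0.2* | *79%* | *40* | *11* | *440 girls". The last three entries are clusters per arm, minimum average students per cluster, and participants per arm.

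**The concern.** Three inputs for one primary outcome disagree within a single section and its table: 80 against 40 clusters, an ICC of 0.2 against 0.15, and 11 against 10 girls per school. The protocol presents the command as the calculation that was done. A colleague who reruns it should get the size in Table 3, and does not. Table 3 also sets a minimum of 440 girls per arm, while the text provides for 500 enrolled × 0.8 = 400 retained. To retain 440 at 20% attrition, 440 / 0.8 = 550 girls per arm would have to be enrolled.

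**Working it through.** **Inputs.** Proportions 0.13 and 0.26, ICC 0.2, alpha 0.05, and beta(0.8) read as 80% power, all from the command. 40 schools per arm from the participants section, the text and Table 3. 10 retained girls per school from the text; 11 from Table 3. Assumed here: a two-sided test, equal cluster sizes, and the normal approximation with pooled variance under the null hypothesis.

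**Formulas.** With n the individually randomised size per arm and ρ the ICC:

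- design effect = 1 + (m − 1)ρ
- effective n = k·m / design effect
- girls per school for fixed k: m = n(1 − ρ) / (k − nρ), rounded up

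**Step 1: size before clustering.** 13% against 26% at 80% power needs n = 145 per arm.

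**Step 2: reproduce Table 3 with k = 40.** m = 145 × 0.8 / (40 − 29) = 116 / 11 = 10.5, rounded up to 11. Then 40 × 11 = 440, exactly the size in Table 3.

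**Step 3: the command as printed, k = 80.** m = 116 / (80 − 29) = 116 / 51 = 2.27, rounded up to 3. Then 80 × 3 = 240 per arm, not 440. Using unpooled variance, a t reference, a continuity correction or 79% target power moves m only between 2.1 and 2.7, so it still rounds to 3. In the other direction, 80 clusters of 11 girls would have 97.9% power, not 79%.

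**Step 4: what k means in this document.** The GBV command (10% against 5%, k = 40, ICC 0.02) has n = 435.

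- k as clusters per arm: m = 435 × 0.98 / (40 − 8.7) = 426.3 / 31.3 = 13.6, rounded up to 14. 40 × 14 = 560, the GBV size in Table 3.
- k as the total over both arms, so 20 per arm: m = 426.3 / (20 − 8.7) = 37.7, rounded up to 38. 20 × 38 = 760, not 560.

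So k is clusters per arm. Reading k(80) as a total would rescue the contraception line, but no single reading of k fits both commands. (Table 3 prints 0.2 as the ICC for GBV. At that value no cluster size works with 40 schools, because 435 × 0.2 = 87 exceeds 40; only the command's 0.02 gives 560.)

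**Step 5: which girl count carries the 79%.** All with 40 schools per arm:

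| Girls per school | ICC | Design effect | Effective n per arm | Power |
|---|---|---|---|---|
| 10 (400 per arm) | 0.2 | 2.8 | 142.9 | 79.5% |
| 11 (440 per arm) | 0.2 | 3.0 | 146.7 | 80.6% |
| 10 (400 per arm) | 0.15 | 2.35 | 170.2 | 86.0% |

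The stated 79% therefore belongs to 10 girls per school at ICC 0.2. With a t reference on 2(k − 1) degrees of freedom the first two rows become 79.3% and 80.3%. The 11 / 440 in the table is the rounded-up answer to the command's 80% target.

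**Sensitivity of the match.** The exact return of 440 depends on the variance formula. With unpooled variance n is about 142, m is 9.8 (10 rounded up), and 10 girls give 80.3% power. With a continuity correction n is 160 and m is 16. The pooled formula, with or without the t reference, is the one that returns both 11 / 440 and a power of 79% at 10 girls.

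**The case against.** The strongest reply is that this is a reporting slip. Eighty is the number of schools over both arms, everything else around it says 40, and the size in Table 3 reproduces from its own row once 40 is used. That stands as an account of how the error arose. It does not make the printed command right, because the GBV line uses k per arm.

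A second reply is that Table 3 gives an ICC for each endpoint, so 0.15 is only a general statement. This largely stands: 0.15 appears in the gender-norms row and 0.2 in both contraception rows. The text nevertheless gives one ICC without qualification, and it is not the one behind the 79%.

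A reader might also infer that Table 3 overstates the girls who will be retained by 40 per arm. The documents do not support that. The column is headed as a minimum, and 440 is what the calculation requires for 80% power; it is not a forecast of retention. The defect is narrower: a required size and an achieved power that belong to different girl counts share one row.

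Nor is it right that the source of the 79% cannot be found. It follows from 40 schools, 10 girls and ICC 0.2.

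**Conclusion.** The point holds in this form. Only k(80) breaks the calculation: as printed it gives 240 girls per arm instead of 440. The Table 3 row joins 11 / 440 (80.6%) to the 79% that belongs to 10 / 400 (79.5%), a difference of about one percentage point. The ICC in the general assumptions is not the one used for this outcome, but the one used is conservative.

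A reader might infer that the study is underpowered for contraception. That is not shown. Under the stated inputs, power with the girls expected is 79.5%, in line with the stated 79%, and a lower ICC would raise it. The result assumes a two-sided 5% test, equal clusters and the pooled normal formula.

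One limit remains after the figures are corrected. Section I words the primary outcome as contraceptive use among sexually active youth, while the power is computed over all girls in the school sample. The corrected 79% describes the second group, not the first.

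**What to change.** 1. In the contraception command, change k(80) to k(40).
2. In the text, state that an ICC of 0.2 was used for contraception, and limit the 0.15 to the endpoints it applies to.
3. In the Table 3 contraception row, either give the expected size (10 girls per school, 400 per arm) with 79%, or label 11 / 440 as the size required for 80% power and show the expected 10 / 400 with 79% beside it.
4. State that this power is computed over all girls in the school sample, not over sexually active youth as the primary outcome is worded.

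The cost is one command, a sentence or two of text and one table row. Enrolment does not change.

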At the beginning of the study, youth aged 10-14 will be enrolled. In Kinshasa, it is not uncommon for a youth to live with a family other than their own either in hopes of broadening horizons or due to family dissolution or orphan status; and thus, youth living in foster families will be eligible to participate. However, where parents are available their consent will be sought. Where participants are orphaned, foster parent or guardian consent will be obtained. Homeless youth will not be eligible to participate due to the likelihood of difficulty with follow-up as well as involvement in intervention programming.

Table 2. Inclusion and exclusion criteria

|  | **Inclusion Criteria** | **Exclusion Criteria** |
| --- | --- | --- |
| **In-school youth** | Males and females between the ages of 10-14 years of age | Not between the ages of 10-14 |
|  | Lives within the geographic boundaries of Kimbanseke or Masina | Does not live within the geographic boundaries of Kimbanseke or Masina |
|  | Lives at home with a family (biological, adoptive, or foster) | Is homeless or lives on the street |
|  | Attends a school selected for the study | Attends a school not selected for the study, or does not attend school |
|  | Able to assent | Unable to assent |
|  | Has obtained informed consent from a parent or guardian to participate in the study | Has not obtained informed consent from a parent or guardian to participate in the study |
| **Parent/guardian of in-school youth** | Parent or guardian of an eligible in-school adolescent who has assented to participate | Not a parent or guardian of a participating in-school adolescent |
|  | Has provided informed consent to participate | Has not provided informed consent to participate |
| **Out-of-school youth** | Males and females between the ages of 10-14 years of age | Not between the ages of 10-14 |
|  | Lives within the geographic boundaries of Kimbanseke or Masina | Does not live within the geographic boundaries of Kimbanseke or Masina |
|  | Lives at home with a family (biological, adoptive, or foster) | Is homeless or lives on the street |
|  | Has not been enrolled in school for 6 or more months | Has not been enrolled in school for fewer than 6 months or is enrolled in school |
|  | Able to assent | Unable to assent |
|  | Has obtained informed consent from a parent or guardian to participate in the study | Has not obtained informed consent from a parent or guardian to participate in the study |

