Initially at baseline descriptive analyses will be done to test for comparability of intervention and comparison groups. Subsequently bivariate statistics (Chi-Square and Student’s t-test) will be run exploring the relationships between independent variables and key outcomes. Finally multivariate analyses will be performed to evaluate associations between gender norms, empowerment and the primary outcomes of interest sexual behaviors and outcomes, gender based violence and mental health. Over time, tests of differences will be run exploring change in gender equitable attitudes, gender norms and how these changes predict changes in prevalence of gender based violence and contraceptive utilization between intervention and control groups.

5. Describe whether you are collecting or storing personal identifiers, and if yes, why you need them, and when and how you plan to dispose of them. Signatures on consent forms are considered to be identifiers.

Participants will be assigned a unique identifier, which will be recorded with their responses during electronic data collection. A separate document containing participant’s photograph, identification number, name, age, and location will be kept in a locked file cabinet at KSPH for data collectors to contact participants for follow-up. These will be retained with consent and assent forms in a dedicated and locked cabinet that will only accessed by the site PI and the study coordinator. All electronic data will be encrypted. All documents with contact information will be destroyed immediately following the last wave of data collection and only coded data without any identifiers will be retained.

6. Answer the following **if they are relevant to your study design**

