1. Describe any potential direct benefits the study offers to participants (“payment” for participation is not a direct personal benefit).

Those in the intervention arm of the study will benefit from an evidence-based program that has been developed and implemented by Save the Children. Previous research suggests that the intervention is effective in increasing gender equitability and shifting gender norm attitudes that benefit participants. We hypothesize that those who will be participants will also be improved contraceptive users and less likely to be perpetrators or victims of gender-based violence.

There is no direct benefit to participants in the control group beyond what has been previously reported as the benefits research subjects feel in being able to share their experiences, exposures and perspectives.

Participants in both groups will be provided a meal and a t-shirt with the study logo.

1. Describe potential societal benefits likely to derive from the research, including value of knowledge learned.

The evidence is that gender-based violence is endemic in the DRC and the direct hypothesized benefit is that the intervention will reduce GBV by 20% and double effective contraception. Additionally, we hypothesize that there will be secondary benefits of more gender equitable relationships between boys and girls in the intervention group, improved mental health outcomes and an increase in healthy sexuality and school retention.

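### The contraception primary outcome is declared for sexually active youth but powered as modern-method use in all girls, so the stated 79% power does not apply to the declared outcome

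*Protocol*

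**What the plan says.** Protocol, Section I (Aims), lists the first primary outcome as "Doubling of contraception use among sexually active youth". It names no class of method and does not limit the outcome to girls. Table 2 in Section IV admits "Males and females between the ages of 10-14 years of age", for both in-school and out-of-school youth.

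The section on sample size and justification describes a different quantity. It states that "The power calculation for contraception is calculated among the girl sample", with 10 girls per school after 20% attrition. Its reference value is worded without a method class: "Baseline contraceptive prevalence in Kinshasa among 15-17 year old adolescents is 13" percent, to be doubled, with 79% power. Table 3 gives the same 13% and the same risk ratio of 2 in a row labelled "Proportion using modern contraception", with 40 clusters per arm, 11 students per cluster, an intra-class correlation of 0.2 and 440 girls per arm. Neither the text nor the table restricts the count to girls who are sexually active.

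The analysis paragraph (Section V.C, item 4) refers only to "contraceptive utilization between intervention and control groups". No section shown defines a modern method, says that the terms are interchangeable, or narrows the declared outcome to girls.

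**The concern.** A primary outcome needs one population, one denominator and one definition of a response. Here the declared outcome and the powered outcome differ on three points:

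- **Sex of the reporter:** youth in the aims, girls in the sample size section and Table 3.
- **Denominator:** sexually active participants in the aims, all girls in the calculation.
- **Method class:** contraception in the aims and the power text, modern contraception in Table 3.

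The denominator matters most. Participants are 10 to 14 at entry and are followed for about four years, so the sexually active may be only part of the cohort. A calculation that counts every girl then credits the analysis with more participants than the declared outcome would use. The sex of the reporter matters too, because the aims wording would let boys' reports into an endpoint that was sized without them. A reader cannot tell which outcome the 79% supports.

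**Working it through.** **Inputs (sample size section and Table 3):** p1 = 0.13, p2 = 0.26, 40 clusters per arm, intra-class correlation 0.2, alpha 0.05 (taken as two-sided). Cluster size after attrition is 10 girls (text) or 11 (Table 3). Table 3 uses 20 per school when both sexes are counted.

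**Formulas.** With k = 40 clusters of size m, the effective number per arm is n_eff = k·m / (1 + (m − 1)·0.2). Power = Φ[((p2 − p1) − 1.96·SE0) / SE1], where SE0 = √(2·p̄(1 − p̄)/n_eff) with p̄ = 0.195, and SE1 = √((p1(1 − p1) + p2(1 − p2))/n_eff).

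**Step 1: the plan's own figure, all girls.**
- m = 10: 400/2.8 = 142.9; SE0 = 0.0469, SE1 = 0.0462; (0.13 − 0.0919)/0.0462 ≈ 0.82; power 79.5%.
- m = 11: 440/3.0 = 146.7; power 80.6%.
- A t-based version with 78 degrees of freedom gives 79.3% and 80.3%.

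The 79% is thus reproduced for the population that the text and Table 3 name: all girls, whether or not sexually active.

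**Step 2: all youth of both sexes.** m = 20: 800/4.8 = 166.7; power 85.3%.

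**Step 3: sexually active only.** The protocol gives no share, so a range is assumed. The rates stay at 13% and 26%; m is 10 (girls) or 20 (both sexes) times the share.

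| Assumed share sexually active | Girls: m, n_eff | Power | Both sexes: m, n_eff | Power |
|---|---|---|---|---|
| 10% | 1, 40.0 | 31% | 2, 66.7 | 47% |
| 20% | 2, 66.7 | 47% | 4, 100.0 | 64% |
| 30% | 3, 85.7 | 58% | 6, 120.0 | 72% |
| 50% | 5, 111.1 | 69% | 10, 142.9 | 80% |

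The last cell for both sexes equals the all-girls result only because half of 20 is 10. The protocol does not argue from such a share.

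**Step 4: dependence on the base of the 13%.** Step 3 treats 13% as the rate among the sexually active. The protocol does not say whether it is that or the rate among all 15-17 year olds. Suppose it is the latter, and only the sexually active use contraception. At a 50% share, the rate among them would be 0.13/0.50 = 26%, doubling to 52%. With n_eff = 111.1, SE0 = 0.0654 and SE1 = 0.0631, so (0.26 − 0.1283)/0.0631 ≈ 2.09 and power is about 98%. With a share below 26%, a doubling would exceed 100% (2 × 0.13/0.26 = 1). The declared outcome therefore has no single power figure until the denominator and its reference rate are stated together.

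**The case against.** The best defence is that the aims use a general term and the table a specific one for the same endpoint. The text and Table 3 share one rate and one risk ratio, which supports reading contraceptive prevalence and modern contraception as the same measure. The list of qualifying methods could sit in the survey instrument, an appendix not shown here, or in an analysis plan. Much of this stands for the method class, which is the mildest of the three differences. It does not explain why sexually active youth became all girls.

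A reader might infer more than the documents support:

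- **That doubling has no fixed starting value.** The calculation states 13% to 26%. What is unclear is the population in which that rate holds.
- **That the benefits section adds a third definition.** Its wording, "the intervention will reduce GBV by 20% and double effective contraception", is a hypothesis about societal benefit and does not define an outcome. At most, its term should be aligned.
- **That girls switching from traditional to modern methods would meet one definition and fail another.** The size of any such split needs a traditional-use rate that the protocol does not give. The aims also do not say that traditional methods count.
- **That boys' and girls' reports will be pooled.** The aims wording permits this, but no section says it will be done.

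**Conclusion.** The concern holds as an internal contradiction about a primary outcome. The aims declare contraception use among sexually active youth; the sample size section and Table 3 power modern-method use among all girls. The stated 79% is sound for the latter (79.5% to 80.6%) and is not a statement about the former.

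At the plan's own rates and intra-class correlation, the figure would be about 85% for all youth of both sexes. For sexually active girls it would run from about 31% to 69% over assumed shares of 10% to 50%. That range rests on two assumptions: the share, for which the protocol has no figure, and 13% as the rate among the sexually active. If the 13% is a rate among all adolescents of that age, the subgroup power could be higher. The finding is therefore that the stated power does not transfer to the declared outcome, and not that the study is shown to be underpowered for it.

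**What to change.** State one contraception primary outcome in the aims, the sample size text and Table 3, and use the same term in the analysis paragraph and the benefits section. It should settle three things:

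1. **Method class.** Modern methods match Table 3; list the methods that count.
2. **Reporter.** Girls reporting on themselves match the stated calculation. Any-method use and boys' reports then become separate secondary outcomes.
3. **Denominator.** Say explicitly whether it is all girls or sexually active girls. Adopting the Table 3 wording must not drop the sexually active restriction from the aims unnoticed.

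If all girls are chosen, the 79% stands and the aims wording changes. If the sexually active restriction is kept, restate the power for that subgroup with an assumed share, and say whether the 13% is a rate among the sexually active or among all girls.

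The cost is protocol wording and, in the second case, one recalculation; recruitment and visits do not change. The downsides are that boys no longer contribute to this primary outcome and that the restated power may be less favourable than 79%.
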